#### Secondary evaluation criteria

In terms of secondary evaluation criteria, we aim to measure seven different endpoints. First, we evaluate the mean change of HbA1c level between baseline and month 18 to observe whether the effects of the intervention lasted in the medium term. Second, HRQoL will be assessed. This measure provides patient-reported information on patients’ daily lives, beyond basic clinical health indicators [26]. The EQ-5D, a generic HRQoL measure, will be used in this study. This tool captures the multidimensional nature of the HRQoL, encompassing the dimensions of physical, mental, and social health [27]. It will be measured at baseline and at months 12 and 18 (mean change) and serve as secondary endpoint.

Third, in a diabetes specific PROM, the DIAB-Q will be used to measure intention to engage in diabetes self-care behaviors [19]. It is a brief (17 items) and psychometrically sound PROM. Besides the application of DIAB-Q to amplify patient-doctor communication in the IG, the mean change between baseline and months 12 and 18 will be used to evaluate if the intention, attitude, and behavior of enrolled patients towards their condition have changed due to the intervention.

Fourth and fifth, the mean change of two clinical measures, namely blood pressure and body composition, between baseline and months 12 and 18 will be used to evaluate the effects of the intervention on patients’ health status. Changes in body composition will be used to quantify changes in response to adapted nutritional habits or physical activity. The literature suggests quantifying body composition using bioelectrical impedance analysis. It has the advantage of being a non-invasive, mobile, portable and reproducible technique. It is based on measuring resistance and reactance in the body. According to the models generally used, body composition can be described in terms of two main compartments, fat mass and lean mass. Lean mass includes water, proteins, and minerals. Muscle mass and organs represent the metabolically active components of lean mass [28].

Sixth, in order to be able to assess changes in patients’ medication (medication intensity) on the basis of claims data, it will be possible to retrospectively assess the change in the number of DDD for anti-diabetic drugs (excl. insulin) according to the A10B anatomical, therapeutic, and chemical classification system (ATC Classification system). Only retrospective data on Groupe Mutuel patients will be available.

Seventh, we collect PREMs to assess patients’ care experience with a brief 9-item outpatient PREM questionnaire which was developed by the New South Wales (Australia) government and adapted to the Swiss context. The following dimensions are measured: satisfaction, subjective experience and objective experience, as well as relations with care providers. PREMs will be measured in months 12 and 18.

Finally, we asses cost-effectiveness of the intervention compared to standard care from payer (health insurance) perspective. The effect measure will be mean change in HbA1c. Cost information will be collected via Groupe Mutuel and participating health care facilities (e.g., intervention costs).

### Participant timeline {13}

Each patient will be participating in the study for 12 months; an additional follow-up measurement is planned after 18 months. Before enrolment of patients, practices are allocated to either the IG or the CG using covariate-constrained cluster randomization. Practices screen their existing patients for eligibility and contact them at their next regular visit. Patients in both groups sign the informed consent at enrolment. Baseline assessment in the IG will be right before their scheduled physician–patient quality circle and at the day of enrolment for patients in the CG. At baseline, participants provide casemix variables, fill in the baseline PROM questionnaires, and PCPs document patients’ medical data. During intervention, medical data, treatment adherence data, and responses to intervention PROMs are collected for patients in the IG. The intervention will take place in the 12 months after baseline and close out with an evaluation at month 12 (short-term) and an evaluation at month 18 (medium-term). Evaluation data collection consists of medical data, evaluation PROMs, and PREMs. Additionally, claims data from Groupe Mutuel are added for respective insurees. For more information on standard protocol items see Table 3.

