#### Step 2: Quality circles, 1-year individualized T2D program for patients, and PRO measurements

The physician–patient quality circles (see Table 2) stand in the center of the intervention and present the starting point for the 1-year individualized T2D program that patients in the IG will follow. The quality circles are organized group sessions with a TPE specialist, the PCP, the study manager, and three to six patients (depending on practice size). Group sessions were chosen due to similar effectiveness compared to individual sessions [4] and their possibility of exchange between participants. Because the session is led by the TPE specialist, the PCP can take a different perspective and change his usual role from a directive to a response-solution approach. Within these sessions, the use of motivational interviewing techniques facilitates communication and patient involvement [23]. By jointly setting clear, motivating goals for patients to improve health and treatment adherence, the outcome of the quality circle is an individualized treatment plan for each patient according to their needs and preferences. The study manager ensures scheduling of activities and visits as well as medical follow-ups.

**Table 2 Tab2:** Design of quality circle

Quality circles	
Objectives	• Change of physicians’ role: Encourage a response and solution approach rather than a directive one • Use of motivational interviewing techniques: Facilitate communication and patient involvement • Definition of learning objectives: Set clear, motivating goals for patients to improve adherence and clinical outcomes
Composition of the quality circle	3–6 patients (depending on practice size), TPE specialist (facilitator), study manager, PCP (recommended presence)
Roles of participants	TPE specialist: • Presentation of TPE elements and lead of quality circle Study manager: • Administrative and operational role (e.g., presentation of potential TPE activities, clinical and psychological follow-up, appointment management) PCP: • Observational role Patient: • Active participation
Timing	At baseline (*t* = 0)
Frequency and duration	1 h 30 m (minimum of one session)
Methods	Quality circles are interactive, enabling dynamic discussions and exchanges between professionals and patients, and among patients
Outcome	Definition of individualized treatment plan based on TPE elements for each patient according to their needs and preferences

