**Table 3 Tab3:**
[figure not shown]
Standard protocol items

Annotations: (1) Baseline assessment for patients in IG before quality circle, for patients in CG at day of enrolment. (2) Only for Groupe Mutuel insurees. *DIAB-Q* Diabetes Intention, Attitude, and Behavior Questionnaire, *EQ-5D-5L* EuroQoL 5-dimension 5-level, *HbA1c* hemoglobin A1C, *PHQ-9* Patient Health Questionnaire, *PROM* patient-reported outcome measure, *PREM* patient-reported experience measure

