### Trial status

The current protocol is version 1, dated December 9, 2024. Recruitment of patients began on June 1, 2025, and will end around December 31, 2025. The study is expected to run until June, 2027.

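### Baseline for the primary change score is taken on the day of enrolment in controls but only before the group quality circle in the intervention arm, after a wait that is neither stated nor capped

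*Protocol article*

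**What the plan says.** The protocol article, Participant timeline {13}, sets the rule: "Baseline assessment in the IG will be right before their scheduled physician–patient quality circle and at the day of enrolment for patients" in the control group. The annotation to Table 3 repeats it: "Baseline assessment for patients in IG before quality circle, for patients in CG at day of enrolment". It is a deliberate rule, stated twice.

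Four other statements bear on it:

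- **Consent and allocation.** In {13}, "Patients in both groups sign the informed consent at enrolment", and earlier, "Before enrolment of patients, practices are allocated to either the IG or the CG using covariate-constrained cluster randomization". Section {17a} says that practices know their arm.
- **Training.** Under Step 1, physicians in the intervention group (IG) are trained first and recruit afterwards.
- **The circle.** Step 2 and Table 2 describe a scheduled session of three to six patients with a TPE specialist and the study manager; Table 2 recommends that the physician attend.
- **Use of baseline.** Under Outcomes {12}, the primary endpoint is the HbA1c change from baseline to month 12. Under Statistical methods {20a}, baseline HbA1c is a fixed effect in the main mixed model.

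The article gives no expected or maximum interval between enrolment and circle, and designates no enrolment HbA1c value in the IG.

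**The concern.** In a randomised comparison of change scores, time zero should mean the same thing in both arms. Here it is consent in the control group (CG) and a later programme event in the IG. Patients are approached one at a time at their next regular visit, whereas the circle is a group appointment, so a gap is to be expected for most IG patients. During it they have agreed to take part and are seen by a trained physician who knows the allocation.

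Two things are at stake. First, any HbA1c change in that gap becomes part of the IG baseline and drops out of the measured change. Adjusting for baseline HbA1c does not repair this, because the covariate is itself taken at a different point in each arm. Second, an IG patient lost between consent and circle leaves no planned baseline, while a control has one on the day of enrolment. The same rule governs the baseline questionnaires, blood pressure and body composition, so the secondary change endpoints share the problem.

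**Working it through.** **1. The plan's own figure.** Inputs from Sample size {14}: difference 0.58, SD 1.10, ICC 0.032, mean cluster size 5, CV 0.30, alpha 0.05 (taken as two-sided), power 0.80, drop-out 15%.

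- Per arm without clustering: 2 × [1.10 × (1.960 + 0.842) / 0.58]² = 56.46
- Design effect: 1 + [(0.30² + 1) × 5 − 1] × 0.032 = 1.1424
- 56.46 × 1.1424 = 64.5; divided by 5 this is 12.9, so 13 clusters, or 65 patients, per arm
- 65 / 0.85 = 76.5, so 77 per arm and 154 in total

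The stated 154 is reproduced, reading 13 clusters as per arm and taking no reduction for matching. It does not depend on when baseline is measured.

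**2. Change during the wait (assumed values; the document gives none).** The standard error of the difference with 65 per arm is 1.10 × √(2 × 1.1424 / 65) = 0.206. If HbA1c falls by d in the IG between consent and circle and the change score misses it:

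| d (points) | share of 0.58 | effect seen | power |
|---|---|---|---|
| 0 | 0% | 0.58 | 0.80 |
| 0.05 | 9% | 0.53 | 0.73 |
| 0.10 | 17% | 0.48 | 0.64 |
| 0.20 | 34% | 0.38 | 0.45 |

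These figures are for the raw change score. In the main model the shift is d times the slope of the month-12 value on baseline. It is smaller if that slope is below one, and zero only if the slope is zero.

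**3. Loss during the wait (also assumed).** Extra IG loss of 0%, 5%, 10% or 15% on top of the planned 15% gives power of 0.81, 0.80, 0.78 or 0.77, so precision is little affected. For bias, if a fraction p of IG patients is lost and their change would have differed by D from that of those who stay, the IG mean shifts by p × D. With p from 0.05 to 0.15 and D from 0.3 to 1.0, the shift runs from 0.05 × 0.3 = 0.015 to 0.15 × 1.0 = 0.15 points, or 3% to 26% of 0.58.

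**4. Direction.** A fall before the circle pulls the estimate towards zero. Losing IG patients who would have done worse pushes it towards the programme. The two need not cancel, and the document fixes neither.

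**The case against.** The best defence is that measuring just before the intervention begins is a recognised choice. The treatment plan is an output of the circle, and the activities and the PROMs at months 3, 6 and 9 follow it. Before it, the only programme element a patient meets is a physician who has had one session of 1 h 30. With about five eligible patients per practice, one circle might serve a whole practice and the wait might be short. All of this is fair, and it is why the 0.1 to 0.2 point fall can be no more than an illustration. It does not remove the asymmetry, because the wait is neither capped nor matched in the CG.

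A reader might infer more than the document supports:

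- **That the arms' changes span different lengths of time.** They do not. Follow-up is 12 months from baseline in both.
- **That season biases the primary endpoint.** Baseline and month 12 fall at the same time of year for each patient.
- **That early loss excludes patients in the IG only.** Sections {11b} and {20c} delete withdrawn patients' data and leave drop-outs out in both arms. What is specific to the IG is a period of possible loss before any planned baseline. Patients who miss the circle without withdrawing are already covered by the stated intention-to-treat rule, and missing values are to be imputed.
- **That late circles overrun the study.** Eighteen months from 31 December 2025 is 30 June 2027, but Trial status gives both the end of recruitment and the end of the study as approximate.
- **That about 5% of IG practices would be too small to hold a circle.** This needs a normal approximation to practice size, and it is a question of feasibility rather than of baseline timing.

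**Conclusion.** The point stands as a design asymmetry that should be removed. Two places in the article tie baseline to consent in one arm and to a later group session in the other, and that baseline is both the start of the primary change score and a covariate. The interval is unknown, so the size and net direction of the bias cannot be set from the document. If circles took place on or near the day of enrolment, the effect would be negligible. Under the assumed falls of 0.1 to 0.2 points it would be 17% to 34% of the 0.58-point effect on the raw change score. The planned sample size of 154 is unaffected.

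**What to change.** Amend Participant timeline {13} and the Table 3 annotation so that HbA1c, blood pressure, body composition and the PROMs are measured on the day of enrolment in both arms, with months 12 and 18 counted from that day. Record the date of each patient's circle.

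For IG patients already enrolled under the current rule, record the interval from enrolment to baseline and run a sensitivity analysis that accounts for it. Do not substitute routine HbA1c values from before enrolment: they may come from assays other than the study device, and they would enter one arm only.

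The cost is a timeline amendment and moving an already planned point-of-care measurement to the enrolment visit. Some IG patients will have had slightly less than 12 months of programme at month 12, which may dilute the effect a little. In return, both arms are compared from the same starting point.

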**Table 3 Tab3:**
[figure not shown]
Standard protocol items

Annotations: (1) Baseline assessment for patients in IG before quality circle, for patients in CG at day of enrolment. (2) Only for Groupe Mutuel insurees. *DIAB-Q* Diabetes Intention, Attitude, and Behavior Questionnaire, *EQ-5D-5L* EuroQoL 5-dimension 5-level, *HbA1c* hemoglobin A1C, *PHQ-9* Patient Health Questionnaire, *PROM* patient-reported outcome measure, *PREM* patient-reported experience measure

### Sample size {14}

The required sample size was calculated based on the expected effect size with respect to our primary endpoint and the specificities of CRTs [29]. We assume an effect size of 0.58 percentage point difference in change of HbA1c between baseline and 12 months in the IG compared to the CG. This assumption is grounded on results from studies with similar intervention designs (e.g., TPEs in individual and group sessions) [4, 6]. Expected distribution (measured by standard deviation) of the primary outcome at baseline is 1.10 [4]; the intraclass correlation is assumed to be 0.032 [30]. From our sample of participating practices, we expect an average size of the cluster of five eligible patients with a coefficient of variation of 30%. We use an a-priori matching before randomization to balance the sample on previously known practice attributes (urban vs. rural location, practice size, specialization of PCP)—we assume a moderate group-level correlation between practice attributes and change in HbA1c [31]. Assuming a commonly used Type 1 error rate (alpha) of 5% and aiming for a power of 80%, the trial requires a minimum of 13 clusters of five patients in each cluster. The sample size was estimated using the sample size calculator of the National Institute of Health [32]. Anticipating a drop-out rate of patients until the end of the trial period of 15% [4], we need to recruit a minimum of 154 patients (77 in the intervention group, 77 in the control group).

### Recruitment {15}

Recruitment of the required practices will be out of the 130 Réseau Delta practices in the Swiss canton of Geneva. Patient recruitment will be carried out by PCPs in the participating practices. Concretely, PCPs will screen their patients for eligibility criteria and approach them at their next visit.

## Assignment of interventions: allocation

### Allocation (sequence generation {16a}, concealment mechanism {16b}, and implementation {16c})

Balanced cluster randomization will be performed by a statistician at the University of St. Gallen who will not be involved in the recruitment or training of practices. Randomization will be based on previously known practice attributes (location, practice size, specialization of PCPs). We use covariate constrained randomization [33] to minimize imbalance from practice attributes. To this end, we employ the cvcrand command in Stata 18, performing 1000 randomizations, and select the allocation that best balances the covariates based on principal component analysis. A clustered permutation test (cptest) is done to test the performance of the randomization.

Group assignments will be implemented through a pre-prepared pseudonymized list of practices provided by Réseau Delta to the University of St. Gallen. Practices are then randomly allocated. The allocation of each of the practices to either intervention or control is marked down in this list, which is then sent back to Réseau Delta who will implement the allocation. The allocation sequence will be securely stored and concealed. The investigator—Réseau Delta—only receives a finalized version of the practice allocation list. Practices will only be informed of their allocation before patient inclusion starts (see Fig. 1). Practices will enter the study arm to which they have been randomly allocated.

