#### Primary endpoint

HbA1c will be analyzed with common descriptive statistics, i.e., sample mean, median, minimum, maximum, standard deviation, and interquartile range. We will follow the intention to treat principle, i.e., all included patients who did not withdraw consent will be analyzed. We will apply two-sample (independent samples) t-tests or Wilcoxon-Mann–Whitney tests (depending on distribution) for the primary endpoint for the mean differences at baseline, month 12 and month 18 and changes in mean difference from baseline to 12 and 18 months. As we anticipate cluster effects at the practice level due to the randomization method, our main model for the assessment of the primary endpoint will be a mixed-effects model. We will control for patient characteristics at baseline (e.g., baseline HbA1c, BMI, gender, age, comorbidities, diabetes duration) as fixed effects, which are likely to affect the primary endpoint. In addition, we will incorporate practice as a random intercept in the model to account for potential cluster effects at the practice level. We will not control for covariate-restricted randomization variables, as differences between practices are accounted for by random intercepts. We use the Wald Test or the Likelihood Ratio Test to evaluate hypotheses on fixed and random effects.

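### The stated allocation rule keeps only the best of 1000 draws, cptest is given a task it cannot do, and omitting the balancing covariates from the model makes the analysis mildly conservative

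*Protocol article*

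**What the plan says.** The Allocation section {16a–16c} of the protocol article makes four statements that bear on each other.

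- The method: "We use covariate constrained randomization [33] to minimize imbalance from practice attributes". The covariates are the practice attributes: "Randomization will be based on previously known practice attributes (location, practice size, specialization of PCPs").
- The selection rule, run with cvcrand in Stata: "performing 1000 randomizations, and select the allocation that best balances the covariates based on principal component analysis". No cut-off, percentile or size of an acceptable set is given.
- The check: "A clustered permutation test (cptest) is done to test the performance of the randomization". Neither the variable tested nor the reference set is stated.
- A general sentence: "Practices are then randomly allocated". It does not say from which set.

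The Primary endpoint part of Statistical methods {20a} says that "our main model for the assessment of the primary endpoint will be a mixed-effects model", tested by Wald or likelihood ratio. It also says: "We will not control for covariate-restricted randomization variables, as differences between practices are accounted for by random intercepts". The Secondary endpoints part likewise leaves these covariates out.

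Sample size {14} assumes a moderate correlation at practice level between these attributes and the change in HbA1c.

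**The concern.** Covariate constrained randomization normally scores many candidate allocations, keeps those that are balanced enough, and draws one of them at random. The retained set then serves as the reference set for a permutation test of the outcome. The rule as written keeps only the best candidate, so the method named and the rule described do not match, and no retained set is available for cptest.

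The purpose given to cptest is also wrong. A clustered permutation test asks whether an outcome differs between arms, relative to the allocations that could have occurred. It does not measure how well the randomization worked; a table of practice attributes by arm does that.

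The third strand is the analysis. Choosing a very well balanced allocation removes most of the chance difference between arms that is due to the three attributes. A random practice intercept does not know this: it still counts the variance those attributes cause among practices as uncertainty in the treatment effect. Intervals come out too wide and the test too cautious. What is at stake is some power and precision, not false positives.

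**Working it through.** **Inputs from the protocol article.** Around 30 practices (Study setting); effect 0.58, SD 1.10, ICC 0.032, mean cluster size 5, coefficient of variation 0.30, alpha 5%, power 80%, drop-out 15% (Sample size). **Assumed:** equal numbers of practices per arm, two-sided alpha, the covariate distributions, an ICC of 0.10 as an alternative, and attributes explaining 50 to 80% of between-practice variance. The article gives no figure for that share.

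**1. The plan's own sample size.** Per arm without clustering: 2 × (1.10 × (1.96 + 0.842) / 0.58)² = 56.46. Design effect: 1 + ((1 + 0.30²) × 5 − 1) × 0.032 = 1.1424. Product 64.5, or 12.9 clusters of five, so 13 clusters (65 patients). 65 / 0.85 = 76.5, so 77 per arm and 154 in total. This matches the plan without any credit for matching, so the point does not touch the 154.

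**2. What the selection rule leaves.** With 30 practices there are C(30,15) = 155,117,520 equal splits; with 26, C(26,13) = 10,400,600. The rule keeps one of 1000 sampled draws. In simulation with continuous practice size, the best draw was unique in at least 99.95% of runs. With all covariates categorical, a median of 31 to 39 of the 1000 draws tied for best, and the article does not say how a tie is resolved.

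**3. Is it still random?** Yes. In 2000 re-runs of best-of-1000 there were 1910 to 2000 distinct allocations. Each practice had a 47 to 52% chance of intervention, and pairs shared an arm with probability 0.33 to 0.62.

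**4. Reference sets for a permutation test.** Type I error at nominal 5% (2000 replicates, Monte Carlo SE about 0.5 points), with attributes explaining 0 / 25% / 50% of the variance of practice means:

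- the selected allocation alone: p = 1 always, so 0 / 0 / 0
- all 1000 draws treated as equally likely: 5.1–5.7% / 1.9–2.9% / 0.5–0.8%
- re-running the whole best-of-1000 procedure: 4.9–5.5% / 4.5–4.8% / 4.1–5.6%

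The unadjusted t-test on practice means behaves like the second line: 5.1–5.5% / 1.9–2.8% / 0.4–0.8%.

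**5. Translating to the plan's ICC.** The variance of a practice mean, in units of total variance, is ICC + (1 − ICC)/5.

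- ICC 0.032: 0.032 + 0.1936 = 0.2256. The between-practice part is 0.032/0.2256 = 14.2%; 50 to 80% of that is R = 7.1 to 11.3%.
- ICC 0.10: 0.10 + 0.18 = 0.28. The between-practice part is 0.10/0.28 = 35.7%; 50 to 80% of that is R = 17.9 to 28.6%.

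So the 25% and 50% columns in step 4 lie beyond what the plan's ICC allows (at most 14.2%).

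With near-perfect balance, the true standard error is √(1 − R) times the unadjusted one, and the actual size is about 2 × [1 − Φ(1.96/√(1 − R))].

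- ICC 0.032: size 4.2 to 3.7%; standard error overstated by a factor of 1.04 to 1.06.
- ICC 0.10: size 3.1 to 2.0%; factor 1.10 to 1.18.

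This is an approximate limiting case, because balance is never exact. Two sets of simulations of the unadjusted test after best-of-1000 gave 3.9–4.6% and 4.1–4.9% at ICC 0.032, and 2.6–3.4% and 2.4–3.0% at ICC 0.10. Adjusting for the three attributes brought the size back to about 5%.

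**The case against.** The best defence has four parts.

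**The article may be abbreviating.** It names the constrained method, cites a source and says practices are randomly allocated. A cut-off and set size could sit in the full protocol. That is possible, but the sentence does more than omit a detail: it states a different rule. The stated purpose of cptest is likewise a misstatement, not an omission.

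**Nothing rests on cptest.** This stands. No endpoint is assigned a permutation test, and the primary inference is "We use the Wald Test or the Likelihood Ratio Test to evaluate hypotheses on fixed and random effects". A p-value fixed at 1 would arise only if the selected allocation alone were the reference set, which the article does not propose.

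**The effect is small and comes from the analysis section.** Largely true. At ICC 0.032 the upper simulated values are hard to tell from 5%. The conservatism arises from good balance combined with an unadjusted model, and drawing from a retained set would not by itself cure it.

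**Allocation is probably done.** Participant timeline {13} places it before enrolment, and Trial status gives June 1, 2025 as the start of recruitment. Advice to redraw is therefore probably moot.

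A reader might go further and infer that randomization-based inference is lost, that no permutation test can be valid here, or that some pairs of practices are forced together or apart. The documents do not support this. The 1000 candidates are themselves random draws, re-running the procedure gives a test of about the right size, and no simulated pair came near 0 or 1. The small share of all possible splits that 1000 draws represents is no defect either.

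**Conclusion.** The point holds in a limited form. The Allocation section describes a best-of-1000 selection under the name of constrained randomization, and gives cptest a purpose it cannot serve. Both should be corrected in the text. The allocation remains random and symmetric between arms, and the primary test is not invalidated.

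The statistical cost is conservatism if the three attributes are prognostic. At the plan's ICC the true size is about 4 to 5% against 5%; at an assumed ICC of 0.10 it is about 2.4 to 3.4%. A permutation over all 1000 draws errs in the same direction. The article's reason for not adjusting, that random intercepts account for differences between practices, does not meet this, because the intercepts absorb the variance without crediting the balance.

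These figures rest on attributes explaining 50 to 80% of between-practice variance, which corresponds to a correlation of √0.5 = 0.71 to √0.8 = 0.89 with the underlying practice effect. If the moderate correlation in the sample-size section is lower on that scale, the size moves closer to 5%. They also use a test on practice means as a stand-in for the mixed model. Patient-level covariates in that model could take up part of the attributes' effect and shrink the discrepancy further.

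**What to change.** 1. If the allocation has been made, keep it and describe it as the best-balanced of 1000 random draws. State the balance score, how ties were resolved and the seed. If a retained set was in fact used, state its cut-off and the random draw from it.
2. Add location, practice size and specialization as fixed effects in the primary mixed model, fixed before outcome data are seen, and delete the sentence that rules this out. Treat the secondary models the same way.
3. Remove cptest as a check of the randomization and report a table of the three attributes by arm.
4. If a permutation p-value for 12-month HbA1c is wanted as a sensitivity analysis, build its reference set by re-running the entire best-of-1000 procedure several thousand times, not from the selected allocation or from the 1000 unselected draws.

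Cost: at least three of about 28 practice-level degrees of freedom (30 practices minus two arms), more if size or specialization has several categories; a short script; and revised wording. The allocation, the 154 patients and the data collected are unchanged.
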